### **Interactions with Subgroups**

Summary tables will be produced for the predefined subgroups and interactions between treatment and these subgroups will be investigated, using a Cox proportional hazards model. A separate model will be used for each interaction to determine its significance. This will also be presented graphically on a forest plot.

The predefined subgroups including:

- Age (<65 years vs. ≥65 years)
- Gender (men vs. women)
- BMI
- Index event (TIA vs. minor ischemic stroke)
- Time from index event to randomization
- Etiological stroke subtype based on the TOAST Classification
- Diabetes mellitus
- Hypertension
- Type of *CYP2Y19* LOF alleles (intermediate metabolizers vs. poor metabolizers)
- Previous ischemic stroke or TIA
- Prior antiplatelet therapy
- Prior statin therapy
- Prior smoking status
- Location of symptomatic artery stenosis (Intracranial artery stenosis vs. extracranial artery stenosis)

### **Secondary Efficacy Analyses**

#### **Rate of new stroke events within 30 days**

The rate of stroke occurring within 30 days will be analyzed using a Cox proportional

hazard model, with the pooled study center as a random effect. This will also be presented graphically on a Kaplan-Meier curve. The hazard ratio with 95% CI will be reported. The log-rank test will be used to evaluate the statistical significance of the treatment effect.

**Rate of new clinical vascular events (ischemic stroke, hemorrhagic stroke, TIA, myocardial infarction, or vascular death) within 3 months**

The rate of new clinical vascular events occurring within 3 months will be analyzed using a Cox proportional hazard model similar to that in the previous section, with the pooled study center as a random effect. A combined vascular event is defined as any of the 5 following events: ischemic stroke, hemorrhagic stroke, TIA, myocardial infarction, or vascular death. This will also be presented graphically on a Kaplan-Meier curve. The hazard ratios with 95% CIs will be reported. The log-rank test will be used to evaluate the statistical significance of the treatment effect.

**Rate of new ischemic stroke within 3 months**

The rate of ischemic stroke occurring within 3 months will be analyzed using a Cox proportional hazard model, with the pooled study center as a random effect. This will also be presented graphically on a Kaplan-Meier curve. The hazard ratio with 95% CI will be reported. The log-rank test will be used to evaluate the statistical significance of the treatment effect.

**Proportion of disabling stroke at 3 months**

The proportion of disabling stroke at 3 months will be analyzed using a logistic regression model. The disabling stroke is defined as Modified Rankin Scale score (mRS) >1. The odds ratio with 95% CI will be reported.

**Incidence and severity of recurrent stroke and TIA during follow-up to 3 months**

Differences in proportion of severity of recurrent stroke and TIA during follow-up to 3 months between the two treatment groups will be tested by Wilcoxon rank sum test. Severity is measured using a six-level ordered categorical scale that incorporates the

mRS: fatal stroke/severe non-fatal stroke [mRS 4 or 5]/moderate stroke [mRS 2 or 3]/mild stroke [mRS 0 or 1]/TIA/no stroke-TIA. The test statistics with p value will be reported.

**Proportion of neurological impairment at 3 months**

The proportion of neurological impairment will be analyzed using a logistic regression model. The neurological impairment is defined as NIHSS increased  $\geq 4$  from baseline. The odds ratio with 95% CI will be reported.

**Quality of life at 3 months follow-up**

Health related quality of life will be measured using EuroQol EQ-5D scale among the survivors. Treatment differences will be tested using student t-test or Wilcoxon rank sum test as appropriate.

**Rate of any new strokes (ischemic stroke or hemorrhagic stroke) within 1 year**

The rate of new stroke (both ischemic and hemorrhagic) reported within 1 year will be analyzed using a Cox proportional hazard model, with the pooled study center as a random effect. This will also be presented graphically on a Kaplan-Meier curve. The hazard ratio with 95% CI will be reported. The log-rank test will be used to evaluate the statistical significance of the treatment effect.

**Rate of new clinical vascular events (ischemic stroke, hemorrhagic stroke, TIA, myocardial infarction, or vascular death) and the individually event within 1 year**

The rate of new clinical vascular events occurring within 1 year will be analyzed using a Cox proportional hazard model, with the pooled study center as a random effect. A combined vascular event is defined as any of the 5 following events: ischemic stroke, hemorrhagic stroke, TIA, myocardial infarction, or vascular death. This will also be presented graphically on a Kaplan-Meier curve. The hazard ratios with 95% CIs will be reported. The log-rank test will be used to evaluate the statistical significance of the treatment effect.

**Rate of new ischemic stroke within 1 year**

The rate of ischemic stroke occurring within 1 year will be analyzed using a Cox proportional hazard model, with the pooled study center as a random effect. This will also be presented graphically on a Kaplan-Meier curve. The hazard ratio with 95% CI will be reported. The log-rank test will be used to evaluate the statistical significance of the treatment effect.

#### **Proportion of disabling stroke at 1 year**

The proportion of disabling stroke at 1 year will be analyzed using a logistic regression model. The disabling stroke is defined as Modified Rankin Scale score (mRS) >1. The odds ratio with 95% CI will be reported.

#### **Incidence and severity of recurrent stroke and TIA during follow-up to 1 year**

Differences in proportion of severity of recurrent stroke and TIA during follow-up to 1 year between the two treatment groups will be tested by Wilcoxon rank sum test. Severity is measured using a six-level ordered categorical scale that incorporates the mRS: fatal stroke/severe non-fatal stroke [mRS 4 or 5]/moderate stroke [mRS 2 or 3]/mild stroke [mRS 0 or 1]/TIA/no stroke-TIA. The test statistics with p value will be reported.

#### **Quality of life at 1-year follow-up**

Health related quality of life will be measured using EuroQol EQ-5D scale among the survivors. Treatment differences will be tested using student t-test or Wilcoxon rank sum test as appropriate.

### **13.Safety Analyses**

All analyses of safety data will be carried out using the safety set (SS) population.

#### **Extent of Exposure**

The extent of exposure will be calculated as the number of days between start of treatment and end of treatment (i.e. treatment stop date – treatment start date + 1), and categorized into months: <1, 1-2, 2-3 months. Exposure will then be summarized by

treatment group.

### **Bleeding Events**

Severe or moderate bleedings (GUSTO definition) at 3 months;

Severe or moderate bleedings (GUSTO definition) at 1 year;

Any bleeding events (severe or moderate bleedings or intracranial hemorrhage) at 3 months and 1 year;

For most bleeding events, the Cox proportional hazards model will be used to compare the hazard ratio (HR) between the two treatments, or Poisson regression or negative binomial regression which are more appropriate for the analysis of rare event.

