|------------------------------------------|-----------------------------------------------------------------------------------------------------------------------------------------------------------------------------------------------------------------------------------------------------------------------------------------------------------------------------------------------------------------------------------------------------------------------------------------------------------------------------------------------------------------------------------------------------------------------------------------------------------------------------------------------------------------------------------------------------------------------------------------------------------------------------------------------------------------------------------------------------------------------------------------------------------------------------------------------------------------------------------------------------------------------------------------------------------------------------------------------------------------------------------------------------|
|                                          | 
categorical scale that incorporates the mRS: fatal stroke/severe non-fatal stroke [mRS 4 or 5]/moderate stroke [mRS 2 or 3]/mild stroke [mRS 0 or 1]/TIA/no stroke-TIA);
 
 
• Neurological impairment at 3 months (NIHSS increased <math>\geq 4</math> from baseline );
 
• Quality of Life (EuroQol EQ-5D scale) at 3 months and at 1 year.
 
 
Safety Outcome Measure
 
1) Primary Safety Outcome Measure:
 
Moderate and severe bleeding events according to the GUSTO criteria at 3-month
 
2) Secondary Primary Safety Outcome Measures:
 
 
• Incidence of severe bleedings or moderate bleedings (GUSTO definition) at 1 year;
 
• All bleeding events (severe/moderate bleeding and intracranial hemorrhage) at 3-month and 1-year;
 
• Total mortality at 3-month and 1-year;
 
• Adverse events/Severe adverse events reported by investigators at 3-month and 1-year.
 
                                                                                             |

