### 11.3 Recording of adverse events

Only some of the non-serious AEs (ie, bleeding events, dyspnea, asthma, renal impairment/increased blood creatinine, bradycardia, increased liver function test indicators, gout/increased uric acid, pneumonia, gynecomastia, abnormal uterine bleeding, malignant tumors) and discontinuations of the study medication due to adverse events (DAEs) will be collected from time of randomization throughout the treatment/follow-up periods to the Study Closure Visit. Other non-serious AEs are up to the investigator to decide whether to collect.

SAE: All SAEs will be collected and recorded.

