**Appendix Table 5. Abnormal clinical laboratory indicators**

|                        |                                                                                                                    |
|------------------------|--------------------------------------------------------------------------------------------------------------------|
| Hemorrhagic tendency   | The prothrombin time was 1.5 times longer than that of the normal control group or platelet $< 10 \times 10^9/L$ . |
| Moderate/severe anemia | Hemoglobin (Hb) $< 90g/L$                                                                                          |
| Hepatic insufficiency  | Aminotransaminase exceeded twice the upper limit of standard level                                                 |
| Renal insufficiency    | Serum creatinine $> 1.5mg/dl$ or creatinine clearance rate $< 50ml/min$                                            |

**Appendix Table 6. Global Utilization of Streptokinase and Tissue Plasminogen Activator for Occluded Coronary Arteries (GUSTO)****bleeding definition**

|                   |                                                                                                                                                                                                                                                                                              |
|-------------------|----------------------------------------------------------------------------------------------------------------------------------------------------------------------------------------------------------------------------------------------------------------------------------------------|
| Severe bleeding   | Including life-threatening bleeding, primary intracranial hemorrhage, post-traumatic symptomatic intracranial hemorrhage that resulted in substantial hemodynamic compromise requiring treatment (blood transfusion, liquid transition, vasoconstrictor medication or surgical intervention) |
| Moderate bleeding | Moderate bleeding was defined by the need for transfusion, but does not reach the standard as severe bleeding; including reduction of absolute value of hemoglobin or red blood cells, causing severe disability or intraocular hemorrhage with severe visual field defect, etc.             |

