| Minor bleeding    | Minor bleeding referred to other bleeding, not requiring transfusion or causing hemodynamic compromise. Including bleeding at the puncture site or hematoma, etc.                                                                                                                            |

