### Primary Safety Endpoint

Incidence of severe bleedings or moderate bleedings (GUSTO definition) at 3 months.

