### Secondary Safety Endpoint

1) Incidence of severe bleedings or moderate bleedings (GUSTO definition) at 1 year;

2) Bleeding events (severe or moderate bleedings or intracranial hemorrhage) at 3 months and 1 year;

3) Mortality within 3 months and 1 year;

4) AEs/SAEs reported by the investigators at 3 months and 1 year.

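### The endpoint labelled all or any bleeding leaves out GUSTO minor bleeding, and no pooled patient-level comparison of total bleeding is planned

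*Supplement*

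**What the plan says.** The endpoint appears in four places in the current versions, always with the same components:

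- SAP v1.3, section 13, Bleeding Events: "Any bleeding events (severe or moderate bleedings or intracranial hemorrhage", at 3 months and 1 year.
- SAP v1.3, section 3, Secondary Safety Endpoint: "Bleeding events (severe or moderate bleedings or intracranial hemorrhage) at 3 months and 1 year".
- Protocol v1.4, synopsis, safety outcomes: "All bleeding events (severe/moderate bleeding and intracranial hemorrhage) at 3-month and 1-year".
- Protocol v1.4, section 4.3: the same components, listed simply as bleeding events.

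The primary safety endpoint (SAP section 3) is "Incidence of severe bleedings or moderate bleedings (GUSTO definition) at 3 months". The same outcome at 1 year is a separate secondary endpoint.

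Protocol Appendix Table 6 defines three GUSTO classes. Severe opens with "Including life-threatening bleeding, primary intracranial hemorrhage". Moderate turns on the need for transfusion. The third class reads "Minor bleeding referred to other bleeding, not requiring transfusion or causing hemodynamic compromise".

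Protocol section 11.3 puts bleeding on the short list of non-serious events that must be collected: "Only some of the non-serious AEs (ie, bleeding events, dyspnea" and others. The secondary objectives (protocol 2.2.4, SAP section 2) list severe or moderate bleeding and bleeding events as two separate items.

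**The concern.** A row headed any bleeding or all bleeding will normally be read as total bleeding. Here it is not: a bleed that is neither severe, moderate nor intracranial does not count.

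The question matters in this trial because the arms differ in the P2Y12 agent, with aspirin given to both for the first 21 days. Protocol section XI names skin and urethral bleeding among the side effects of ticagrelor, and nosebleeds and gum bleeding among those of aspirin. Where such bleeds need no transfusion and cause no haemodynamic compromise, they are GUSTO minor. The protocol background also reports more non-CABG, non-procedure-related major bleeding with ticagrelor than with clopidogrel in an earlier coronary trial. Total bleeding by arm is thus a natural safety question. The separate objective on bleeding events appears to pose it, but no endpoint answers it.

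**Working it through.** The point concerns a definition, and the plan gives no figure for it to reproduce. The check is to set the components side by side.

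| Type of bleed | Primary safety endpoint (severe or moderate) | Composite labelled all/any bleeding | Other between-arm comparison |
|---|---|---|---|
| GUSTO severe | yes | yes | AE/SAE tables |
| GUSTO moderate | yes | yes | AE/SAE tables |
| Intracranial, graded severe or moderate | yes | yes | AE/SAE tables |
| Intracranial, outside severe and moderate | no | yes | AE tables, if recorded as an AE |
| GUSTO minor, not intracranial | no | no | AE tables only |

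**Step 1: overlap at 3 months.** The composite is the primary safety endpoint plus the fourth row. How large that row is depends partly on how Appendix Table 6 is read. The severe definition goes on, after primary intracranial haemorrhage, to post-traumatic symptomatic intracranial haemorrhage with haemodynamic compromise requiring treatment. If that qualifier governs only the last item, every primary intracranial haemorrhage is already severe. If it governs the whole list, fewer are. On either reading, Appendix Table 1 defines haemorrhagic transformation separately and includes an asymptomatic form, which can fall outside severe and moderate. MRI with GRE-T2*/SWI within 72 hours of randomization (section 10.2.4) could detect it. The overlap is heavy by definition but not complete.

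**Step 2: what is left out.** The fifth row enters none of the bleeding endpoints in protocol 4.3 or in SAP sections 3 and 13.

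**Step 3: whether another analysis supplies a total.** The Adverse Events part of SAP section 13 compares arms by system organ class and preferred term with Fisher's exact test. That classification spreads skin, nasal, gum, urinary and gastrointestinal bleeds over different rows. A patient with two kinds of bleed appears in two rows, and no row counts patients with any bleed. Protocol 13.3.2 promises a comparison of adverse reactions in general terms and defines no bleeding total.

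**Step 4: illustration on assumed rates.** The documents give no bleeding rates, so these figures show only how power depends on event frequency. They do not size the omission. Inputs: n = 6,396/2 = 3,198 per arm, two-sided 0.05, assumed clopidogrel-arm risk p1, assumed ticagrelor-arm risk p2, and p̄ = (p1 + p2)/2.

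Power = Φ{[|p1 − p2| − 1.96·√(2p̄(1 − p̄)/n)] / √[(p1(1 − p1) + p2(1 − p2))/n]}

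For p1 = 1% and p2 = 2%: (0.010 − 1.96 × 0.003040)/0.003037 = 1.331, and Φ(1.331) = 91%.

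| Assumed p1 | Risk ratio 1.5 | Risk ratio 2 |
|---|---|---|
| 0.2% | 12% | 31% |
| 0.5% | 25% | 64% |
| 1% | 44% | 91% |
| 2% | 73% | over 99% |
| 3% | 89% | over 99% |

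If severe and moderate bleeding prove rare, the planned bleeding endpoints could miss a doubling of risk. A more frequent total-bleeding endpoint with the same risk ratio would have more power.

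**The case against.** Centring the safety analysis on severe, moderate and intracranial bleeding is a defensible focus on serious harm. The primary safety endpoint does not depend on this composite. All four places spell out the components, and only two of them carry the word all or any.

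Three stronger readings are tempting, and the documents do not support them.

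- **The composite adds nothing to the primary safety endpoint.** A reader might infer this from the severe definition. Haemorrhagic transformation, including the asymptomatic form, and other intracranial bleeds outside severe or moderate may add events, and no rates are given to show how many.
- **Minor bleeding is ignored, so an excess in one arm would be hidden.** Non-serious bleeding must be collected and is asked about at discharge, day 21, day 90 and month 12. AEs at 3 months and 1 year are a secondary safety endpoint and are tested by arm. What is missing is the pooled count of patients.
- **The data are already graded, so only wording is at issue.** Sites are trained in the GUSTO criteria and overt bleeds are adjudicated, but no section says that every non-serious bleed receives a GUSTO class.

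What remains is that two labels promise more than the definition delivers, and that no planned analysis pools severe, moderate and minor bleeding per patient.

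**Conclusion.** The point holds in this form. Followed as written, the plan would report an all or any bleeding comparison that excludes GUSTO minor bleeding, and it contains no pooled patient-level comparison of total bleeding. The definition is the same in four places across the current protocol and SAP, so it is not a slip in one of them. The composite overlaps heavily with the primary safety endpoint without duplicating it.

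The size of the omission cannot be stated from the documents, and the power figures above rest on assumed rates and risk ratios. The conclusion itself rests only on the listed components and on the AE analysis being done by organ class and term, as described. Efficacy inference and the primary safety endpoint are unaffected. The change should be made because total bleeding is a relevant comparison here and the bleeding events it needs are collected.

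**What to change.** In the SAP (sections 3 and 13) and the protocol (synopsis and section 4.3):

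1. Define any bleeding as GUSTO severe, moderate or minor, at 3 months and 1 year. Count patients with at least one such bleed, and use the same model as for the other bleeding endpoints.
2. Add GUSTO minor bleeding as its own line.
3. Rename the present composite as severe, moderate or intracranial bleeding.
4. Report intracranial haemorrhage separately as well. Among the current bleeding endpoints it has no line of its own and enters this composite as a component.

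The cost is amended wording and a few added table rows. The real work is that any non-serious bleed not already graded on the CRF must be assigned a GUSTO class, and this must be finished before unblinding. No new data collection appears to be needed, since bleeding events are already on the required list.

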### **Adverse Events**

Adverse events (AEs) will be coded using the MedDRA coding dictionary (Version 6.0 or a later release) and grouped by system organ class (as detailed in the study protocol).

Separate data display listings and summaries will be presented for adverse events that start prior to first dose of study medication (pre-treatment), whilst on study medication (during treatment) and after the last dose of study medication (post-treatment).

Within each treatment group, the number and percentage of subjects experiencing an AE will be summarized by system organ class and preferred term and Fisher's Exact test will be used to compare the number of each grouped AE event between treatment groups. In addition, a separate summary will be provided for AEs experienced by more than 5% of subjects in either of the treatment groups.

### **Deaths and Serious Adverse Events**

Summary tables and data displays will be provided for serious adverse events (as detailed in the study protocol). In addition, all deaths and serious AE's will be documented in a case narrative format in the clinical study report.

The number of deaths occurring over the treatment period will be summarized and Fisher's Exact test will be used to compare the number of deaths between treatment groups.

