### **11.2 Definitions of adverse events**

#### **11.2.1 Adverse event (AE)**

Adverse Events, regardless of their relationship to Investigational Product, as long as they occur from the first visit planned in the Clinical Trial Protocol/signature of the informed consent (i.e., occurring during the washout period) to the last visit planned in the protocol, are adverse medical events or deterioration of qualifying event. AEs include symptoms (ie, nausea, chest pain), signs (ie, tachycardia, liver enlargement) and abnormal laboratory results (ie, laboratory or ECG abnormalities). AEs can be classified as serious AEs and non-serious AEs.

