#### **11.2.2 Serious adverse event (SAE)**

A Serious adverse event is refers to any untoward medical occurrence that at any

dose:

- Results in death, or
- Is life-threatening, or

**Note: The term “life-threatening” in the definition of “serious” refers to an event in which the patient is at risk of death at the time of the event; it does not refer to an event which hypothetically might have caused death if it was more severe.**

- Requires inpatient hospitalization or prolongation of existing hospitalization, or
- Results in persistent or significant disability/incapacity, or
- Is a congenital anomaly/birth defect, or
- Is a medically important event

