#### **13.4 Interim analysis**

Interim analysis will focus on patient recruitment, baseline comparability of treatment arms, sample size assumptions with regard to event rates, loss to follow-up, adverse effects data, and effect of treatment on the primary endpoints. We will plan one interim analysis when 60% of total patients ~~had~~ have undergone randomization and completed follow-up. The sample size will be inflated to account for one interim analyses of the primary efficacy outcome with the use of an O'Brien–Fleming spending function, and a p value of less than 0.008 will be considered significant. In the final analysis, a p value of less than 0.048 will be considered statistically significant. Trial investigators will be blinded to the results of interim analysis.

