### ***Interim Analyses***

Data and Safety Monitoring Board (DSMB) is in place to ensure the safety of subjects in the study. An independent statistician will prepare summary statistics on enrollment, subject status in the study, baseline characteristics, and safety data, including summary tables of coded SAEs and these will be examined by the DSMB. These tables will be provided to the DSMB at regular intervals. If the tables give rise to safety concerns for

any treatment, the DSMB may recommend that the trial should be modified or stopped prematurely. The Steering Committee will, in conjunction with the sponsor, decide whether to act on this recommendation.

The interim analysis is based on the stopping boundaries calculated by the Lan-DeMets method with an O'Brien-Fleming type alpha spending function. One interim and one final analysis are planned to be conducted. We planned one interim analysis when 60% of total patients had undergone randomization and completed follow-up. Let  $p_0$  and  $p_1$  be the proportion of primary outcome (new stroke) for the control and intervention group respectively. Let  $d = p_0 - p_1$  and  $\hat{d}$  be the observed difference. The following table lists the stopping boundaries for the interim analysis.

Table. Interim analysis for testing  $H_0: d=0$  vs  $H_a: d \neq 0$

| Stage | Expected sample size* | Boundary value | Rule                                                                                    | Type I error achieved |
|-------|-----------------------|----------------|-----------------------------------------------------------------------------------------|-----------------------|
| 1     | 3838                  | 0.035          | If $ \hat{d}  > 0.035$ , reject $H_0$ and stop;
otherwise continue to the next stage | 0.008                 |
| 2     | 6396                  | 0.023          | If $ \hat{d}  > 0.023$ , reject $H_0$ and stop;
otherwise stop, accept $H_0$         | 0.048                 |

Note: \* indicates the sample size is adjusted for 5% of loss of follow-up over 3 months

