## 6. Sample size estimates

The study hypothesized that there is no difference in 90-day risk of stroke (ischemic or hemorrhagic) in those treated with a 3-month regimen of ticagrelor initiated with a loading dose of 180 mg followed by 90 mg bid compared with a 3-month regimen of clopidogrel initiated with a loading dose of 300 mg followed by 75 mg/d when therapy is initiated within 24 hours of symptom onset in patients with TIA or minor ischemic

stroke carried *CYP2C19* LOF allele treated with aspirin 75 mg/d.

The minimum necessary sample size in the trial is established by the requirement to detect the smallest expected, clinically meaningful treatment difference comparing the treatment with placebo. Based on the genetic sub-analysis of the CHANCE study, we presume that the 90-day risk of stroke recurrence in *CYP2C19* loss-of-function allele carriers is about 9.4%, and 6.7% for noncarriers. With the point-of-care identification of the *CYP2C19* loss-of-function allele carriers to assess a proper pharmacogenetic approach for patients with high-risk TIA or MIS, we assumed a 25% relative risk reduction with alteration from clopidogrel to ticagrelor (90-day risk of stroke recurrence: 7.1%). Considering the potential impact of the interim analyses on the probability of type I error, we adjusted the statistical significance to a 2-sided  $\alpha$  of 0.048. With a sample size of 6,396 patients, we will have 90% power to detect a relative risk reduction (Ticagrelor: loading dose: 180mg, 90mg bid on day 2-90 vs. Clopidogrel: loading dose: 300mg, 75mg qd on day 2-90) of 25% and 5% dropouts (medication nonadherence). Assuming 58.8% prevalence of *CYP2C19* loss-of-function allele carriers in a Chinese population, we projected screening 10,878 patients would be necessary. Based on the results of interim analysis, the DSMB will recommend whether the sample size need to be re-calculated.

According to the DSMB meeting on April 7, 2021, the DSMB lookup the overall event rates of the trial and suggested not to unblind the treatment assignment in the interim analysis. Therefore, comparison of efficacy and safety outcome between two treatment groups were not performed in the interim analysis, and sample size was not re-calculated. The type I error level of the statistical significance will be set to a 2-sided  $\alpha$  of 0.05 in the final analysis.

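### Efficacy endpoint events also count as serious adverse events, so an overall SAE total mixes benefit with harm; add a comparison of SAEs other than ischemic efficacy events

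*Supplement*

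**What the plan says.** - **Definition.** Protocol v1.4 section 11.2.1 counts events between consent and the last planned visit whatever their relation to study drug; these "are adverse medical events or deterioration of qualifying event". Section 11.2.2 makes an event serious if, among other criteria, it kills, disables, is medically important or "Requires inpatient hospitalization or prolongation of existing hospitalization".
- **Capture.** Protocol section 11.3 has all SAEs collected. For non-serious events only a named list is mandatory. Neither protocol v1.4 nor SAP v1.3 exempts stroke, TIA, MI or vascular death.
- **Endpoint.** SAP v1.3 section 3 lists as a secondary safety endpoint "AEs/SAEs reported by the investigators at 3 months and 1 year". Protocol section 4.3 does the same.
- **Comparison.** The safety analysis text in protocol section 13.3.2 says that secondary safety endpoints will be compared between the two arms. SAP section 13, under Deaths and Serious Adverse Events, says that "Summary tables and data displays will be provided for serious adverse events", and names a test only for deaths.
- **DSMB.** SAP section 5, Interim Analyses, gives the board safety data at regular intervals, "including summary tables of coded SAEs and these will be examined by the DSMB".

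**The concern.** A new stroke will usually meet at least one seriousness criterion. If ticagrelor prevents strokes, its SAE total falls for that reason alone. A finding that total SAEs were similar or fewer on ticagrelor would then partly repeat the efficacy result and say less than it seems to about harm.

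This matters most for serious events with no endpoint of their own. Protocol section XI lists dyspnea among the ticagrelor risks, for example. Bleeding and death have dedicated analyses. A diffuse excess of other serious events has no dedicated endpoint apart from the SAE total.

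**Working it through.** **Inputs from the documents.** Stroke risk on clopidogrel 9.4% and on ticagrelor 7.1% at 90 days (SAP section 6); 6,396 patients, 90% power, 5% dropout (same section); 1:1 allocation (protocol section 7.2), so 3,198 per arm; two-sided alpha 0.048 for the sample size.

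**Inputs not in the documents, assumed here.** Non-stroke SAE risk b on clopidogrel, 1% to 10%. Share f of strokes reported as SAEs, 50% to 100%. Stroke SAEs and other SAEs are taken to occur in different patients.

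**1. The plan's own figure.** Two proportions with pooled variance under the null, no continuity correction: 3,038 per arm, 6,076 in total. Then 6,076 / 0.95 = 6,396, which matches.

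**2. Strokes per arm at the design rates.** 3,198 × 0.094 = 301 on clopidogrel and 3,198 × 0.071 = 227 on ticagrelor. The difference is 3,198 × 0.023 = 74 patients, or 2.3 points.

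**3. Offset in the SAE total.** The offset is f × 0.023 × 3,198: 74 patients at f = 100%, 55 at 75%, 37 at 50%.

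**4. Relative excess that leaves the total equal (f = 100%).** The ratio is (b + 0.023) / b. Excluding strokes, Fisher's exact test compares the non-stroke SAE counts.

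| Assumed b | Non-stroke SAEs, clopidogrel vs ticagrelor | Ratio | p, strokes excluded | p, all SAEs |
|---|---|---|---|---|
| 1% | 32 vs 106 | 3.3 | 1e-10 | 1.0 |
| 3% | 96 vs 169 | 1.8 | 6e-6 | 1.0 |
| 5% | 160 vs 233 | 1.5 | 0.0002 | 1.0 |
| 10% | 320 vs 393 | 1.2 | 0.004 | 1.0 |

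**5. Excess needed to show significant harm (two-sided 0.05, b from 1% to 10%).** In the all-SAE total: 125 to 138 patients (3.9 to 4.3 points). In non-stroke SAEs alone: 19 to 50 patients (0.6 to 1.6 points).

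**6. One example, b = 3% and a 1.5-fold excess.** Non-stroke SAEs are 96 vs 144 (3.0% vs 4.5%), Fisher p = 0.002. Adding all strokes gives 397 vs 371 (12.4% vs 11.6%), p = 0.34, now numerically in favour of ticagrelor. With half of the strokes reported, the total is 246 vs 258 (7.7% vs 8.1%), p = 0.61.

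These figures cover 3 months. The documents give no stroke rate for 1 year, so no 1-year figure is computed.

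**The case against.** **No pooled SAE test is specified.** A reader might infer that SAP section 13 plans one. It does not: it promises tables, and the comparison comes from the general sentence in protocol section 13.3.2. Neither text says what the compared SAE quantity is. This stands. It narrows the point to an endpoint whose content is undefined and whose simplest form would be a mixture.

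**Other outputs separate strokes from other harm.** A reader might infer that harm in general could be hidden. SAP section 13 models GUSTO bleeding, tests deaths, tabulates and tests adverse events by system organ class and preferred term, and requires a narrative for every serious event. Protocol section 11.4 bases its total AE rate on events judged at least possibly drug-related. This largely stands: masking is limited to the overall SAE total. However, the term-level tests are stated for adverse events and not for SAEs, testing term by term splits a diffuse excess into small cells, and narratives are not a comparison.

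**The DSMB sees coded tables.** A reader might infer that the board could not tell strokes from other SAEs. The tables are coded, so it could. Only an uncoded overall count would carry the mixture.

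**The size rests on assumptions.** It does. The documents give neither the non-stroke SAE rate nor the share of strokes reported as SAEs, and the offset also supposes that the full design effect is achieved.

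**Excluding every efficacy event would discard harm.** This also stands. The primary endpoint includes hemorrhagic stroke, which protocol section XI lists as a ticagrelor side effect, and vascular death includes death from stroke. Only ischemic efficacy events should be set aside.

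**Conclusion.** The point holds in limited form. The documents do not exempt efficacy endpoint events from SAE reporting, and they make SAEs a compared secondary safety endpoint without saying which SAEs form the comparison. At the design effect, an overall total would absorb up to about 74 patients (2.3 points) of other SAEs on ticagrelor, or about 37 if half of strokes are reported. That the strokes enter the SAE count is inferred from the definitions and is not stated outright.

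The documents do not support the stronger conclusion that the safety analysis as a whole would conceal harm. Primary efficacy and primary safety conclusions are not affected. What is at stake is the reading of one secondary safety endpoint, and the change is worth making because it is cheap.

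**What to change.** In SAP section 13, under Deaths and Serious Adverse Events:

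- State whether efficacy endpoint events are reported as SAEs.
- Add a between-arm comparison of SAEs that excludes adjudicated ischemic efficacy events: ischemic stroke, MI, and vascular death not due to hemorrhage.
- State how TIA is classified, because the adjudication list in protocol section 15.1 does not name it.
- Keep hemorrhagic stroke and all bleeding, including fatal hemorrhage, in this comparison.
- Count events to 3 months and to 1 year, as the endpoint states, and show the result beside the all-SAE total.

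Give the DSMB the same split, using the investigator's classification where adjudication is pending.

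The cost is SAP wording and one extra table. Site reporting of SAEs does not change. The drawback is that the new comparison relies on event classification, which is why the all-SAE total should stay beside it.
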